## Abstract

**Background:**

It is unclear whether different modes of continuous renal replacement therapy (CRRT) impact post-filter ionized calcium concentrations during regional citrate anticoagulation (RCA) when using calcium-containing replacement fluid.

**Methods:**

This prospective, single-center, observational cohort study will screen all patients receiving CRRT for eligibility. General clinical information will be collected before commencing CRRT treatment. Patients will be randomly assigned to either the continuous veno-venous hemofiltration (CVVH) or continuous veno-venous hemodialysis (CVVHD) group and switch to the alternative mode in the subsequent treatment session. Pre-filter and post-filter ionized calcium, systemic total and ionized calcium, and effluent total calcium will be measured 2 h after the initiation of CRRT. Electrolyte levels, arterial blood gases, hourly citrate dose, and total citrate dose will be recorded every 6 h until the end of CRRT. The primary outcome is the difference in ionized calcium concentrations at each site over time between the two modes.

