### CRRT parameter setting and management

PrismaFlex (Baxter Investment Co., Ltd, Chicago, IL) CRRT device and AN69 ST150 hemofilters (Baxter Investment Co., Ltd, Shanghai, China) will be used. Vascular access will be established by inserting a double-lumen catheter (SCW Medication Ltd, certification number: 20173664588, 12 Fr, 20 cm) into either the femoral or internal jugular vein. CRRT will be ended for any of the following reasons: achievement of therapeutic goals; coagulation of the filter; transmembrane pressure continuously > 250 mmHg; or continuous treatment for 48 h (to replace pipeline and filter).

This study is a before-after design in the same patient; each patient will receive both continuous veno-venous hemofiltration (CVVH) and continuous veno-venous hemodialysis (CVVHD) at least once. Patients will be initially randomized into either the CVVHD or CVVH groups and then crossed over to the other group during the second CRRT session. Regardless of whether CVVH or CVVHD is used, the initial settings will be as follows: blood flow rate of 150 ml/min, 4% sodium citrate flow rate of 230 ml/h, 10% calcium gluconate infusion rate of 10 ml/h, and a 5% sodium bicarbonate infusion rate (ml/h) of dialysate/replacement fluid × 0.0625 − 120. The therapeutic dose will be 30 ml/kg/h depending on the mode investigated, that is, a dialysate rate (ml/h) of 30 ml × body weight (kg) in the setting of CVVHD; on the other hand, the replacement fluid rate (ml/h) will be 30 ml × body weight (kg) in the setting of CVVH.

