The clinician will assess whether to adjust the CRRT parameters based on arterial blood gas and post-filter iCa concentration two hours after the start of CRRT. No adjustment of the citrate dose is required, and post-filter iCa levels will be monitored every four to six hours if the therapeutic goal of anticoagulation is achieved (post-filter iCa concentration 0.20–0.4 mmol/L). If anticoagulation is not achieved, the citrate infusion rate will be adjusted according to Table 1, and post-filter iCa levels will be monitored every two hours until the therapeutic goal is achieved. The goal of systemic iCa will be between 1.00 and 1.20 mmol/L. The 10% calcium gluconate infusion rate will not be adjusted, and arterial blood gas will be monitored every four to six hours if serum iCa concentration reaches the target. The calcium gluconate infusion rate will be adjusted according to Table 2, and arterial blood gas will be monitored every two hours until the target is reached if serum iCa concentration does not reach the target.

**Table 1. t0001:** Adjustment of 4% sodium citrate infusion rate according to post-filter ionized calcium level.

Post-filter iCa (mmol/L)	Change in citrate infusion rate
<0.2	20ml/h ↓
0.2–0.4	No change
0.41–0.45	10ml/h ↑
>0.45	20ml/h ↑

**Table 2. t0002:** Adjustment of calcium gluconate infusion rate according to systemic ionized calcium level.

Systemic ionized Ca^2+^ (mmol/L)	Change in 10% calcium gluconate infusion rate
>1.35	5ml/h ↓
1.2–1.35	2ml/h ↓
1.0–1.2	No change
0.91–0.99	2ml/h ↑
0.86–0.90	5ml/h ↑
0.75–0.85	7.5 ml/h ↑
<0.75	10ml/h ↑

If circuit clotting is detected, the circuit will be discontinued immediately to ensure patient safety. All clotting events will be documented in detail, including the time of detection, last recorded post-filter iCa level, circuit running time before clotting, and citrate dose at the time of clotting. The attending physician will then evaluate the patient’s clinical condition to determine whether immediate CRRT re-initiation is necessary or if CRRT can be temporarily discontinued until the next scheduled treatment. If clinical assessment indicates the need for immediate CRRT continuation, a new circuit will be initiated following the standard protocol. Given the short half-life of citrate, the time required for circuit replacement is believed to be sufficient to eliminate any carry-over effects.

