### Study objectives

The primary objective is to evaluate trends in post-filter iCa2+, pre-filter iCa effluent iCa2+ and total calcium, systemic iCa2+, and total calcium concentration over time in different RCA-CRRT modes.

The secondary objectives are to analyze the amount of citrate used in different modes to achieve the desired anticoagulant effect in current clinical practice, and to assess the incidence of new-onset metabolic complications (hypercalcemia, hypocalcemia, metabolic acidosis, metabolic alkalosis, citrate accumulation, hypernatremia, hyponatremia). The incidence of metabolic complications will be calculated as the number of new-onset metabolic complication events per 100 CRRT days. In this study, citrate accumulation is defined as the presence of a total serum calcium/ionized calcium ratio > 2.5.

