### Sample size

According to the results of our pilot study, the post-filter iCa concentration was 0.44 mmol/L in the CVVHD mode and 0.305 mmol/L in the CVVH mode. Assuming a standard deviation of 0.2 mmol/L, taking a *α* = 0.05 and a *β* = 0.10, the required sample size is 26 cases. Thirty patients will be included in the study considering the possible loss of follow-up.

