There are several limitations to this study. First, it will only compare the differences in iCa changes between CVVH and CVVHD at each time point, thus not providing information on iCa concentration changes in combined modes (e.g. continuous veno-venous hemodiafiltration, CVVHDF) with varying dialysate and replacement fluid ratios. In other words, this study focuses exclusively on CVVH and CVVHD modes. While CVVHDF is increasingly used in severe AKI patients, we chose CVVH and CVVHD as our initial investigation platforms to establish the fundamental principles in more controlled settings. This strategic approach will serve as a stepping stone for future studies investigating more complex CRRT modalities such as CVVHDF. Second, plasma citrate concentrations will not be measured in this study, making it impossible to directly compare differences in plasma citrate concentrations.

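### The primary outcome compares ionized calcium over time, but citrate and calcium are titrated to common targets from 2 h, so later readings understate the mode effect; the untitrated 2 h value is not named as primary.

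*Protocol article*

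**What the plan says.** The abstract defines the primary outcome: "The primary outcome is the difference in ionized calcium concentrations at each site over time between the two modes". The Study objectives section puts it as trends: "The primary objective is to evaluate trends in post-filter iCa2+, pre-filter iCa effluent iCa2+ and total calcium, systemic iCa2+, and total calcium concentration over time". The limitations paragraph of the Discussion says of the study that "it will only compare the differences in iCa changes between CVVH and CVVHD at each time point". None of these names one site or one time as primary.

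The section on CRRT parameter setting and management fixes a common start: "Regardless of whether CVVH or CVVHD is used, the initial settings will be as follows: blood flow rate of 150 ml/min", with citrate at 230 ml/h and calcium gluconate at 10 ml/h. The first decision to adjust follows: "The clinician will assess whether to adjust the CRRT parameters based on arterial blood gas and post-filter iCa concentration two hours after the start of" treatment. Citrate stays as it is "if the therapeutic goal of anticoagulation is achieved (post-filter iCa concentration 0.20–0.4 mmol/L"); otherwise, "If anticoagulation is not achieved, the citrate infusion rate will be adjusted according to Table 1", with rechecks every 2 h until the target is met. Table 2 does the same for systemic iCa through calcium gluconate, with a goal of 1.00–1.20 mmol/L.

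The Data collection section schedules the multi-site calcium sample at 2 h of each new circuit. The Sample size section rests on one variable: "the post-filter iCa concentration was 0.44 mmol/L in the CVVHD mode and 0.305 mmol/L in the CVVH mode", with SD 0.2, α 0.05 and β 0.10, giving 26 patients, raised to 30. Citrate use is a secondary objective.

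**The concern.** From 2 h onward, post-filter and systemic iCa are controlled quantities. Staff change an infusion in response to them until they fall in a band that is the same for both modes. A comparison of those values estimates the mode effect after correction, whereas the Introduction asks whether mode itself changes post-filter iCa. The Introduction also says that post-filter iCa is the basis for setting the citrate dose, so the feedback is known to the authors but is not reflected in the primary outcome.

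At stake is the headline result. A real effect of mode could be reported as small because it was corrected at the bedside. The variable that absorbs the correction, citrate dose, would sit among the secondary results and might not be read together with iCa.

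**Working it through.** **1. The plan's own figure.** Inputs from the Sample size and Statistical analysis sections: difference 0.44 − 0.305 = 0.135 mmol/L; SD 0.2; two-sided α 0.05; power 0.90; paired t-test.
- Normal approximation: n = (0.2 × (1.960 + 1.282) / 0.135)² = 23.06, so 24.
- Paired t (noncentral t): power is 89.9% at n = 25 and 91.1% at n = 26.

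The stated 26 is reproduced, with 0.2 acting as the SD of within-patient differences. With 30 patients power is 94.7%. The calculation covers one variable at one unspecified time.

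**2. Direction of the titration.** Setting the pilot means against Table 1:

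| Mode | Pilot mean | Table 1 row | Action on citrate |
|---|---|---|---|
| CVVHD | 0.44 | 0.41–0.45 | up 10 ml/h |
| CVVH | 0.305 | 0.2–0.4 | none |

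The rule acts mainly on the mode expected to be higher and moves it toward the other. Individual sessions below 0.2 are moved up by the same table, which also narrows the gap.

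**3. Which sample escapes.** Starting settings are the same in both modes, the first adjustment decision is made at 2 h, and the multi-site sample is drawn at 2 h of each new circuit. That sample precedes the first scheduled adjustment. Every later one can follow an adjustment.

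**4. Possible size of the attenuation.** Table 1 was simulated from the two pilot means, rechecking every 2 h off target and every 6 h on target. Assumptions not in the article: post-filter iCa falls by 0.005–0.03 mmol/L per 10 ml/h of citrate; within-patient SD 0.03–0.14; between-patient SD 0.05; measurement noise 0.02.

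| Time | Mean CVVHD − CVVH difference (mmol/L) |
|---|---|
| 2 h | about 0.135 |
| 6 h | 0.08–0.12 |
| 12 h | 0.05–0.11 |
| 24 h | 0.04–0.095 |
| 48 h | 0.03–0.08 |

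Loss by 48 h runs from (0.135 − 0.082)/0.135 = 39% to (0.133 − 0.034)/0.133 = 74%. The lost part reappears as 27–145 ml/h more citrate in CVVHD at 48 h.

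**5. What this does to power.** Suppose the CVVHD mean is pulled to 0.40 and CVVH stays at 0.305, a difference of 0.095. With the SD kept at 0.2, power at n = 26 is 64%. But the SD cannot stay at 0.2 if both values lie in the band. Differences then lie within ±0.20, and at a mean of 0.095 the largest SD is √((0.20 − 0.095) × (0.20 + 0.095)) = √0.030975 = 0.176, which gives power 75%. With SD 0.10, power is 99.6%. Smaller differences at SD 0.10 give 84% (0.06) and 31% (0.03).

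In the simulated settings whose 2 h SD is near the planned 0.2 (within-patient SD 0.14), difference and SD shrink together. At 24 h the pairs run from 0.090 with SD 0.137 (power 90%) to 0.040 with SD 0.076 (power 73%). The bias in the estimate is therefore clear, and the loss of power is uncertain.

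**The case against.** The strongest reply is that iCa under routine titration is a legitimate pragmatic question. The Discussion openly puts clinical applicability first, and citrate needed to reach target is already a secondary objective, so the displaced effect is recorded. This stands in part: the over-time comparison is worth reporting. It does not answer the stated aim, however, which concerns the influence of mode on post-filter iCa, and the plan does not say that later iCa is to be read together with dose.

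Four stronger readings that a reader might infer are not supported.
- *That titration erases the difference.* Table 1 makes no change inside 0.20–0.40, so a gap can persist within the band, and in the simulation it never reached zero.
- *That power falls to 64%.* That figure keeps the SD at 0.2, which is impossible once both values are in the band.
- *That the stated 90% power is refuted.* The article does not say when the pilot values were taken or whether citrate had already been adjusted.
- *That the primary carries a 26% family-wise error* (1 − 0.95⁶ = 0.265). This assumes six independent measures, whereas these are linked calcium measures. Pre-filter and effluent sampling is scheduled only at 2 h, so a full grid of analyte-by-time tests is not in the article. Multiplicity handling may also lie in an analysis plan that is not shown.

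The 2-hourly versus 4–6-hourly intervals are bedside monitoring. Research recording is at 2 h and then 6-hourly, although post-filter iCa is not named in the 6-hourly list.

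**Conclusion.** The point holds as one of attenuation. A primary outcome defined over time includes readings taken under feedback rules that push both modes into the same post-filter and systemic bands, so those readings understate the mode effect. The direction follows from the article's own tables and pilot means. The size does not: a loss of roughly 40–75% of the difference by 48 h rests on assumed slopes and SDs, and any loss of power rests on an SD under titration that the article does not give. The 2 h comparison is unaffected. There the planned 0.135 is detectable with 91% power at n = 26, on the assumption that 0.135 is itself an untitrated difference and 0.2 is the SD of paired differences. The defect is that no statement of the primary outcome or objective selects that comparison.

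**What to change.** Define one primary endpoint: post-filter iCa at 2 h in the first circuit of each mode, sampled before any change under Table 1 or Table 2. Use the same definition in the abstract, the Study objectives and the limitations paragraph. State in the Sample size section when the pilot values were measured and whether citrate had been adjusted by then. If it had, the 0.135 needs to be reconsidered for the 2 h endpoint. Make the other sites and all later times secondary, and say that later iCa will be interpreted jointly with citrate and calcium gluconate dose.

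The cost is wording. The 2 h sample is already scheduled, the dosing rules stay as they are, and the sample size stands if the pilot values prove to be untitrated. What is given up is the over-time comparison as a primary result.

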**Discussion:**

This study will build upon clinical practice to explore the differential effects of various CRRT modes on ionized and total calcium in patients undergoing RCA-CRRT with calcium-containing replacement solutions.

## Introduction

Over the past decade, the prevalence of acute kidney injury (AKI) has increased significantly. The Kidney Disease Improving Global Outcomes (KDIGO) guidelines indicate that more than 50% of patients in the intensive care unit (ICU) have AKI, with approximately 10% of them requiring renal replacement therapy (RRT) [1,2]. Regional citrate anticoagulation (RCA) is widely used in continuous renal replacement therapy (CRRT) due to its low risk of bleeding and extended filter life [3–11].

Ionized calcium (iCa) is a crucial cofactor activating the coagulation cascade. Citrate acts as an anticoagulant by chelating iCa to form a stable calcium-citrate complex [12–14]. Post-filter iCa level is crucial for the adjustment of the citrate dose: the citrate dose is initially set based on an appropriate citrate dose/blood flow ratio and subsequently adjusted according to the post-filter iCa concentration to maintain a target iCa between 0.20 and 0.40 mmol/L in the circuit (equivalent to a blood citrate concentration of 3–4 mmol/L) in the clinical practice [15,16].

Commercial calcium-containing replacement solutions are increasingly used in CRRT and have a higher iCa concentration than conventional replacement solutions [17–19]. Due to the different mechanisms of solute removal, there could theoretically be apparent differences in post-filter iCa and even systemic calcium when different CRRT modalities are used [20]. For example, in hemodialysis, solutes move with a concentration gradient, and a high concentration of iCa in the dialysate may gradually diffuse into the blood, increasing post-filter iCa (Figure 1A); in contrast, in hemofiltration, the solute and solvent move simultaneously with the pressure gradient, and the post-filter iCa concentration is unlikely to increase (Figure 1B). Since the post-filter iCa concentration is the basis for adjusting the dose of citrate, the potential difference in the post-filter iCa concentration under the different CRRT modalities using calcium-containing replacement solutions may lead to markedly different citrate dosages, even a different incidence of adverse events such as citrate accumulation and citrate toxicity [21–24].

**Figure 1. F0001:**
[figure not shown]
Theoretical trends of ionized calcium movement in different renal replacement therapies. Panel A: In hemofiltration, solute and solvent move from blood to effluent across a semipermeable membrane (dotted line) in response to transmembrane pressure. For citrate-anticoagulated blood, iCa concentration (solid dots) should be identical on both sides of the membrane, with a typical iCa of approximately 0.4 mmol/L. Panel B: In hemodialysis, the iCa concentration of calcium-containing dialysate (approximately 1.5 mmol/L) is much higher than the level of iCa in the citrate anticoagulated blood (approximately 0.4 mmol/L); therefore, iCa moves with the concentration gradient from the dialysate to the blood, resulting in an increase in post-filter iCa, which in turn may affect the efficacy of citrate anticoagulation.

However, the effect of citrate on post-filter iCa concentrations was investigated in the context of calcium-free replacement solutions in previous studies [25,26]. There is little data to show whether different CRRT modes can affect post-filter iCa concentrations during RCA-CRRT using calcium-containing replacement fluid. We hypothesize that a dialysis-based CRRT mode would increase post-filter iCa concentrations and citrate requirements. The present study aims to explore the influence of different CRRT modes on the post-filter iCa concentration in patients receiving RCA-CRRT using calcium-containing replacement fluid.

## Patients and methods

### Study design

This is a prospective, single-center, cross-over, observational cohort study in patients treated with RCA-CRRT. The study was registered at the ClinicalTrials.gov on 26 Aug 2023 (version 1.0, NCT06021080). The study protocol is reported according to the SPIRIT guidelines [27].

### Study setting and population

The study setting is the Surgical Intensive Care Unit (22 beds) of Fujian Provincial Hospital (2500 beds), Fujian Medical University, Fujian Province, China. All patients admitted to the ICU who need RCA-CRRT will be screened for study eligibility.

The inclusion criteria are 1) Age ≥ 18 years old; 2) Receiving citrate anticoagulation; 3) Informed consent obtained from patients or next of kin.

The exclusion criteria are 1) Pregnant or lactating women; 2) Allergic to citrate anticoagulants; 3) Severe liver dysfunction (total bilirubin levels exceeding two times the normal range); 4) Hypoxemia (PaO_2_ < 60 mmHg); 5) Inadequate tissue perfusion (blood pressure < 90/60 mmHg despite high doses of vasoactive agents); 6) Hyperlactatemia (lactate> 4 mmol/L); 7) Hypernatremia; 8) Estimated length of hospital stay < 48h; 9) Participated in other studies.

### Preparation of the replacement solution and citrate

A commercially available calcium-containing replacement solution will be used (Qingshan Licang Pharmaceutical Co, Chengdu, China, certification number: H20080452). When this product is used in combination with a 5% sodium bicarbonate injection (250 ml NaHCO_3_ for a 4000 ml bag), the concentration of each component is as follows: Na+ 141 mmol/L, Ca^2+^ 1.5 mmol/L, Mg^2+^ 0.75 mmol/L, Cl^-^ 110 mmol/L, Glucose 10.6 mmol/L, HCO_3_^−^ 35 mmol/L. During RCA-CRRT, the pre-blood pump infuses 4% trisodium citrate solution (Qingshan Licang Pharmaceutical Co, Chengdu, China, certification number: H20045612) into the extracorporeal circuit’s arterial line. In addition, T-branches will be connected at the end of the venous line, one for blood sampling and the other for connection to the sodium bicarbonate injection. To prevent the sodium bicarbonate from reacting with the calcium gluconate, the 10% calcium gluconate will be pumped into the body *via* a central venous line (peripherally inserted central catheter, subclavian catheterization, or internal jugular vein catheterization).

### CRRT parameter setting and management

PrismaFlex (Baxter Investment Co., Ltd, Chicago, IL) CRRT device and AN69 ST150 hemofilters (Baxter Investment Co., Ltd, Shanghai, China) will be used. Vascular access will be established by inserting a double-lumen catheter (SCW Medication Ltd, certification number: 20173664588, 12 Fr, 20 cm) into either the femoral or internal jugular vein. CRRT will be ended for any of the following reasons: achievement of therapeutic goals; coagulation of the filter; transmembrane pressure continuously > 250 mmHg; or continuous treatment for 48 h (to replace pipeline and filter).

This study is a before-after design in the same patient; each patient will receive both continuous veno-venous hemofiltration (CVVH) and continuous veno-venous hemodialysis (CVVHD) at least once. Patients will be initially randomized into either the CVVHD or CVVH groups and then crossed over to the other group during the second CRRT session. Regardless of whether CVVH or CVVHD is used, the initial settings will be as follows: blood flow rate of 150 ml/min, 4% sodium citrate flow rate of 230 ml/h, 10% calcium gluconate infusion rate of 10 ml/h, and a 5% sodium bicarbonate infusion rate (ml/h) of dialysate/replacement fluid × 0.0625 − 120. The therapeutic dose will be 30 ml/kg/h depending on the mode investigated, that is, a dialysate rate (ml/h) of 30 ml × body weight (kg) in the setting of CVVHD; on the other hand, the replacement fluid rate (ml/h) will be 30 ml × body weight (kg) in the setting of CVVH.

The clinician will assess whether to adjust the CRRT parameters based on arterial blood gas and post-filter iCa concentration two hours after the start of CRRT. No adjustment of the citrate dose is required, and post-filter iCa levels will be monitored every four to six hours if the therapeutic goal of anticoagulation is achieved (post-filter iCa concentration 0.20–0.4 mmol/L). If anticoagulation is not achieved, the citrate infusion rate will be adjusted according to Table 1, and post-filter iCa levels will be monitored every two hours until the therapeutic goal is achieved. The goal of systemic iCa will be between 1.00 and 1.20 mmol/L. The 10% calcium gluconate infusion rate will not be adjusted, and arterial blood gas will be monitored every four to six hours if serum iCa concentration reaches the target. The calcium gluconate infusion rate will be adjusted according to Table 2, and arterial blood gas will be monitored every two hours until the target is reached if serum iCa concentration does not reach the target.

**Table 1. t0001:** Adjustment of 4% sodium citrate infusion rate according to post-filter ionized calcium level.

Post-filter iCa (mmol/L)	Change in citrate infusion rate
<0.2	20ml/h ↓
0.2–0.4	No change
0.41–0.45	10ml/h ↑
>0.45	20ml/h ↑

**Table 2. t0002:** Adjustment of calcium gluconate infusion rate according to systemic ionized calcium level.

Systemic ionized Ca^2+^ (mmol/L)	Change in 10% calcium gluconate infusion rate
>1.35	5ml/h ↓
1.2–1.35	2ml/h ↓
1.0–1.2	No change
0.91–0.99	2ml/h ↑
0.86–0.90	5ml/h ↑
0.75–0.85	7.5 ml/h ↑
<0.75	10ml/h ↑

If circuit clotting is detected, the circuit will be discontinued immediately to ensure patient safety. All clotting events will be documented in detail, including the time of detection, last recorded post-filter iCa level, circuit running time before clotting, and citrate dose at the time of clotting. The attending physician will then evaluate the patient’s clinical condition to determine whether immediate CRRT re-initiation is necessary or if CRRT can be temporarily discontinued until the next scheduled treatment. If clinical assessment indicates the need for immediate CRRT continuation, a new circuit will be initiated following the standard protocol. Given the short half-life of citrate, the time required for circuit replacement is believed to be sufficient to eliminate any carry-over effects.

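### The initial bicarbonate formula, combined with the 30 ml/kg/h fluid rule, gives a negative rate for every patient under 64 kg, so this one starting setting is undefined for them

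*Protocol article*

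**What the plan says.** All the rules that matter here are in the protocol article.

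- **Bicarbonate rate** (CRRT parameter setting and management): the starting value is a "5% sodium bicarbonate infusion rate (ml/h) of dialysate/replacement fluid × 0.0625 − 120". The sentence that contains it opens with "Regardless of whether CVVH or CVVHD is used, the initial settings will be as follows", so the formula applies in both modes.
- **Fluid rate** (same section): "The therapeutic dose will be 30 ml/kg/h depending on the mode investigated". This is spelled out as "a dialysate rate (ml/h) of 30 ml × body weight (kg) in the setting of CVVHD" and, for the other mode, "the replacement fluid rate (ml/h) will be 30 ml × body weight (kg) in the setting of CVVH".
- **Mixing ratio** (Preparation of the replacement solution and citrate): the replacement solution is combined with 5% sodium bicarbonate at "250 ml NaHCO_3_ for a 4000 ml bag".
- **Eligibility** (Study setting and population): "The inclusion criteria are 1) Age ≥ 18 years old; 2) Receiving citrate anticoagulation; 3) Informed consent obtained from patients or next of kin". None of the nine exclusion criteria concerns body weight.

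The article does not explain the constant 120, state a weight range for the formula, set a floor at zero, or say what to do when the result is negative.

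**The concern.** The bicarbonate rate depends on the fluid rate, and the fluid rate depends on weight. With a fixed 120 ml/h subtracted, a light enough patient gets a rate below zero, which no pump can deliver. The question is whether that happens at weights an adult ICU would actually see.

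If it does, one of the standardised starting settings does not exist for part of the eligible population, and bedside staff must decide what to run. Bicarbonate delivery acts on acid-base status. The Discussion names blood pH and acid-base status among the influences on ionized calcium, which is the primary measure, and metabolic acidosis and alkalosis are among the secondary endpoints. A starting rate left to individual interpretation could therefore add uncontrolled variation to both.

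**Working it through.** **Inputs, all from the protocol article**

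- Fluid rate F = 30 × W ml/h, with W the body weight in kg, in CVVH and in CVVHD.
- Initial bicarbonate rate B = F × 0.0625 − 120 ml/h.
- Mixing ratio 250 ml bicarbonate to 4000 ml solution.
- No weight limit in the eligibility criteria.

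**Step 1: is the multiplier as intended?** 250 / 4000 = 0.0625. The factor in the formula agrees exactly with the stated mixing ratio, so it is not a typing slip. The constant 120 cannot be derived from anything in the article.

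**Step 2: substitute the fluid rule.** B = 30 × W × 0.0625 − 120 = 1.875 × W − 120 ml/h. B is zero when W = 120 / 1.875 = 64 kg, that is, at a fluid rate of 30 × 64 = 1920 ml/h.

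| Weight (kg) | Fluid rate (ml/h) | Fluid × 0.0625 | Bicarbonate rate (ml/h) |
|---|---|---|---|
| 40 | 1200 | 75.0 | −45.0 |
| 50 | 1500 | 93.75 | −26.25 |
| 55 | 1650 | 103.1 | −16.9 |
| 60 | 1800 | 112.5 | −7.5 |
| 64 | 1920 | 120.0 | 0 |
| 70 | 2100 | 131.25 | +11.25 |
| 80 | 2400 | 150.0 | +30.0 |
| 100 | 3000 | 187.5 | +67.5 |

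**Step 3: does another reading rescue it?**

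- Bracketing as F × (0.0625 − 120) gives a negative rate at every weight.
- Counting the 230 ml/h citrate flow as part of the fluid, which the text does not say, moves the zero point to (1920 − 230) / 30 = 56.3 kg. The problem shrinks but remains.

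**Step 4: how many patients?** The article gives no weight distribution, so this step rests on assumption. With normally distributed weights, the share below 64 kg is Φ((64 − mean) / SD):

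| Assumed mean (SD), kg | z | Share below 64 kg |
|---|---|---|
| 60 (10) | 0.40 | 66% |
| 65 (12) | −0.08 | 47% |
| 70 (12) | −0.50 | 31% |
| 75 (15) | −0.73 | 23% |

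With the planned 30 patients, that range is about 30 × 0.66 ≈ 20 down to 30 × 0.23 ≈ 7.

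**The case against.** The strongest reply is practical: a pump cannot run backwards, so staff will take a result at or below zero to mean no bicarbonate at the start. That may be the intention, but the article does not say so. Ignoring the subtraction or setting a rate by judgement would be equally open to a clinician. A full protocol that is not shown might contain a floor. Even so, this is more than a detail lost in condensation, because the article prints two specific rules that cannot both be followed below 64 kg.

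Several stronger conclusions might be drawn, and the documents do not support them.

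- **That the starting settings as a whole fail.** They do not. Blood flow, citrate, calcium gluconate and the fluid rate itself can all be set at any weight. Only the bicarbonate setting fails.
- **That the primary comparison is biased.** The formula is identical in both modes and each patient is their own control. At an unchanged weight it gives the same result in both sessions, so consistent handling would be the same on both sides of the comparison. Different handling between sessions is possible, since bedside clinicians and nurses know the mode, but nothing in the article shows that it would occur. Bicarbonate also enters at the end of the venous line, downstream of the filter, so any effect on pre- or post-filter ionized calcium would be mainly indirect, through systemic acid-base status.
- **That the deviation would go unchecked.** Parameters are reassessed on arterial blood gas at two hours, blood gases and electrolytes are recorded every 6 h, and the Discussion says that these parameters will be used as covariates. This limits the consequences but does not define the starting rate.
- **That Table 2 contains a comparable contradiction.** Its rows share the boundary value 1.2. However, the text states "The goal of systemic iCa will be between 1.00 and 1.20 mmol/L" and uses Table 2 only when the target is not reached, so a value of 1.20 calls for no change. The shared boundary is clerical at most.

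**Conclusion.** The inconsistency is real and exact. Two rules in the same section combine to 1.875 × W − 120 ml/h, which is negative for every weight below 64 kg. Patients below that weight are eligible, and the article says nothing about a negative result. For them, the initial bicarbonate setting cannot be carried out as written.

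The 64 kg threshold needs no assumption beyond the printed formulas. The share of patients affected does: 23% to 66% is a range over assumed weight distributions, not an estimate for this ICU.

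The statistical consequence is conditional. If lighter patients are handled inconsistently, acid-base status will vary for reasons outside the design. That could add variation to ionized calcium and affect the counts of acidosis and alkalosis. Bias in the within-patient comparison is not shown. The sample size and the planned tests do not depend on this formula.

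**What to change.** The sponsor's clinical team should reconcile the bicarbonate formula with the 30 ml/kg/h flow rule, and explain or correct the constant 120, so that the starting setting is defined for every eligible weight. Which of the two rules should change, and how, is a clinical decision; no rate or rule is proposed here.

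The bicarbonate rate actually given should be recorded in every session, so that departures can be described by mode and considered alongside the acid-base covariates already planned.

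The cost is a short protocol amendment with ethics committee approval and one more item on the case report form. The sample size and the analysis methods are unchanged.
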